## Abstract

**Background:**

Telerehabilitation has been proposed as an adjunct/alternative to standard center-based cardiac rehabilitation. Two recent systematic reviews showed non-inferiority and/or superiority of this remote approach for cardiac rehabilitation. However, these trials focused only on one core component of cardiac rehabilitation and telemonitoring, rather than implementing a more comprehensive approach. The aim of Telerehab III is to investigate the long-term effectiveness of the addition of a patient-tailored, internet-based telerehabilitation program implementing multiple cardiac rehabilitation core components and using both telemonitoring and telecoaching strategies to standard cardiac rehabilitation.

**Methods/Design:**

In this prospective, multi-center randomized, controlled trial 140 patients with coronary artery disease and/or chronic heart failure patients will be recruited between February 2013 and February 2015. Patients will be randomized 1:1 to an intervention group (receiving an internet-based telerehabilitation program in addition to standard cardiac rehabilitation) or to standard cardiac rehabilitation alone. The mean follow-up is at least 6 months. The primary endpoint is peak oxygen consumption (VO2 peak). Secondary endpoints include measured and self-reported daily physical activity, cardiovascular risk factor control, health-related quality of life, days lost due to (non)cardiovascular rehospitalizations and time to first (non)cardiovascular rehospitalization. A clinical event committee blinded to treatment allocation assesses causes of rehospitalizations.

**Discussion:**

Telerehab III will be one of the first studies to examine the added value of a more comprehensive cardiac telerehabilitation program, focusing on multiple cardiac rehabilitation core components. It has the potential to augment current standard center-based cardiac rehabilitation practices and to be used as a model for other disease prevention programs.

**Trial registration:**

Current controlled trials ISRCTN29243064. Registration date 21 January 2015.

## Background

Secondary prevention of cardiovascular disease (CVD) by means of cardiac rehabilitation (CR) is a Class IB recommendation by the European Society of Cardiology (ESC), the American Heart Association (AHA) and the American College of Cardiology [1]. It is comprised of different core components such as (increase in) physical activity, behavioural change, risk factor modification, nutritional counselling and stimulation of psychosocial wellbeing [2, 3]. However, despite the proven clinical effectiveness of conventional supervised center-based CR (improvements in CVD risk factors, physical activity and physical fitness) [4], long-term benefits are often disappointing due to lack of adherence and persistent change in lifestyle [5, 6]. In addition, patients regularly choose not to attend in-hospital rehabilitation sessions due to a lack of access to transport, ill-health, time and scheduling commitments associated with returning to work or reimbursement issues. It thus follows that suboptimal secondary CVD prevention emerges. Therefore, new strategies or innovations in adjunct/addition to CR, that would lead to increased participation rates and long-term therapy adherence, are urgently warranted.

Recent technological innovations in ICT can be a potential adjunct and/or alternative to enhance rehabilitation adherence and hence long-term effectiveness of CR programs. In telerehabilitation and -prevention, the patient is not restricted to the hospital or rehabilitation center environment for CR, but rehabilitates remotely by using one or several devices monitoring and communicating patient-specific information to the caregivers.

Two recent systematic reviews regarding cardiac telerehabilitation programs showed non-inferiority and/or superiority of this approach, when compared to conventional center-based supervised CR [7, 8]. However, in most studies only one or two of the CR core components (physical activity, behavioural change, risk factor modification, nutritional counselling and psychosocial wellbeing) were integrated in the studied intervention. Telemonitoring and telecoaching were the two focus areas mostly applied, the use of combined approaches and tailoring to the patients’ needs was limited. This demonstrates the need for the implementation of a more comprehensive telerehabilitation program.

The Telerehab III trial is a randomised, controlled, multi-center study designed to investigate the long-term effectiveness of the addition of a patient-tailored, internet-based telerehabilitation program implementing multiple CR core components and using both telemonitoring and telecoaching strategies to conventional CR; when compared to conventional center-based CR alone. The primary hypothesis is that the addition of telerehabilitation increases patient’s physical fitness and activity level with greater magnitude, when compared to usual care. Secondary endpoints include cardiovascular risk factor control, quality of life and (non-) cardiovascular rehospitalizations.

## Methods/Design

### Study design

Telerehab III is a multi-center, prospective, randomized, controlled clinical trial recruiting one hundred and forty stable coronary artery disease (CAD) and/or chronic heart failure (CHF) patients (Fig. 1). Patients are randomized in equal proportions to one of two groups: internet-based telerehabilitation in addition to center-based rehabilitation (intervention group) or center-based rehabilitation alone (control group). Patients are enrolled after completion of the first six weeks of their phase II center-based rehabilitation program. They are followed for a minimum of 6 months and a maximum of 25 months.

**Fig. 1 Fig1:**
[figure not shown]
Flow chart for patient inclusion and follow-up. Screening, inclusion and exclusion, randomization and tests at baseline and follow-up. CR: Cardiac Rehabilitation; IPAQ: International Physical Activity Questionnaire; HeartQol: quality of life questionnaire; EQ-5D: EuroQol questionnaire; CPET: CardioPulmonary Exercise Testing; TTE: TransThoracic Echocardiography

Patients are recruited from the Cardiology Departments of three Belgian hospitals i.e. Jessa Hospital (Hasselt), Ziekenhuis Oost-Limburg (Genk) and St. Franciscus Hospital (Heusden-Zolder). The Jessa Hospital acts as the coordinating center for the trial. Each participating site is responsible for the recruitment and scheduled follow-up visits of patients; but also for contingency patient management. Each site recruits at least ten patients.

The study is conducted in accordance with the principles stated in the Declaration of Helsinki (reviewed version of 2008), local and national regulations. Written informed consent is obtained from all patients prior to study enrollment. The study is approved by the appropriate ethics committee prior to study enrollment, (Jessa Ethics Committee; reference number: B243201216043).

The study adheres to the relevant standards of reporting. A completed CONSORT checklist can be found in Table 1. There were no important changes to the methods after trial commencement.

**Table 1 Tab1:** Completed CONSORT checklist for Telerehab III

Section/Topic	Item No	Reported in section
Title and abstract		
	1a	
	1b	See abstract. No results and conclusions yet since study design paper
Introduction		
Background and objectives	2a	See Background
	2b	See Background
Methods		
Trial design	3a	See Methods (Study design)
	3b	See Methods (Study design)
Participants	4a	See Methods (Study population)
	4b	See Methods (Study design)
Interventions	5	See Methods (Study intervention)
Outcomes	6a	See Methods (Study endpoints)
	6b	See Methods (Study endpoints)
Sample size	7a	See Methods (Sample size)
	7b	See Methods (sample size)
Randomization:		
Sequence generation	8a	See Methods (Randomization)
	8b	See Methods (Randomization)
Allocation concealment mechanism	9	See Methods (Randomization)
Implementation	10	See Methods (Randomization)
Blinding	11a	See Methods (Study endpoints)
	11b	Not applicable
Statistical methods	12a	See Methods (Statistical analysis)
	12b	See Methods (Statistical analysis)
Results		
Participant flow	13a	Not yet available (since study design paper)
	13b	Not yet available (since study design paper)
Recruitment	14a	See abstract
	14b	Not applicable
Baseline data	15	Not yet available (since study design paper)
Numbers analysed	16	Not yet available (since study design paper)
Outcomes and estimation	17a	Not yet available (since study design paper)
	17b	Not yet available (since study design paper)
Ancillary analyses	18	Not yet available (since study design paper)
Harms	19	Not yet available (since study design paper)
Discussion		
Limitations	20	Not yet available (since study design paper)
Generalisability	21	Not yet available (since study design paper)
Interpretation	22	Not yet available (since study design paper)
Other information		
Registration	23	See Trial registration
Protocol	24	See Main manuscript
Funding	25	See Acknowledgements

### Study population

Patients belonging to one of the two cardiac disease categories (ia CAD for which patients were treated conservatively, with a percutaneous coronary intervention or with coronary artery bypass grafting OR ib CHF with reduced EF (NYHA I, II and III) OR ic CHF with preserved EF (NYHA I, II and III)) and who had signed the informed consent form; are eligible to participate. All patients were on optimal medical treatment and stable for >4 weeks. In addition, eligible patients are at least 18 years and maximally 80 years old. They must have a personal computer with internet connection.

The main exclusion criteria are: the presence of a pre-existing non-cardiovascular condition (orthopedic and/or neurological), limiting the patient’s ability to actively engage in exercise training; the presence of terminal disease, dementia and cognitive impairment that unables the patient to use the telerehabilitation equipment or appear to follow-up visits. The complete list of inclusion and exclusion criteria is provided in Table 2.

**Table 2 Tab2:** Summary of key inclusion and exclusion criteria for Telerehab III

Inclusion criteria
ia. CAD patients treated conservatively, with PCI or CABG.
ib. CHF patients with reduced EF
ic. CHF patients with preserved EF
ii. Current active rehabilitation on one of the recruiting centres
iii. Possesion of personal computer with internet connection
iv. Age >18 and <80 years
v. Familial with Dutch language
vi. Informed consent
Exclusion criteria
i. Orthopaedic and/or neurological condition, limiting the patient’s ability to actively engage in exercise training sessions
ii. Impairment to use the telerehabilitation equipment or appear at follow-up visits (terminal disease, dementia and cognitive impairment)
iii. Simultaneous participation in anoter clinical trial
iv. Patients with CHF NYHA IV
v. Patients with a history of VF. exertional sustained VT/supraventricular tachycardia within the previous 6 months

*CAD* coronary artery disease, *CHF* chronic heart failure, *PCI* percutaneous coronary intervention, *CABG* coronary artery bypass grafting, *EF* ejection fraction, *NYHA* New York Heart Association, *VF* ventricular fibrillation, *VT* ventricular tachycardia

### Sample size

The sample size calculation is based on a 20 % effect size of VO2 peak , which is comparable to the effect reported by Frederix et al. in their Telereab II study [9]. In order to attain a minimal power of 95 %, at an alpha error probability < 0,05; 140 patients should be recruited when taking into account a dropout rate of 30 % during follow-up.

### Randomization

Patients are assigned to one of two treatment arms by a central computerized randomization system. Block randomization is used to ascertain equal distribution of patients in the intervention and control group in the different recruiting hospitals. In order to achieve a balance of relevant patient characteristics in both study arms, it will be assessed whether patients are matched for age, gender, cardiac disease category and cardiovascular risk factor profile. When intervention and control patients are not matched for these characteristics, a second randomization process will be done to ascertain matching. Investigators are unaware of the randomization sequence.

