### Statistical analysis

The statistical analysis will be performed according to the Intention-to-treat principle. For continuous data, the Shapiro-Wilk test will investigate whether normal distribution is present. When data are not normally distributed, the Mann–Whitney U-test will be used for the comparison between groups; and the Wilcoxon Signed Rank test will be used for the comparison within groups. When data are normally distributed the One Way ANOVA repeated measures test will be used for both between and within group analysis. Kaplan-Meier plots and log-rank tests will be used to compare censored time-to-event data; for the time to first cardiovascular rehospitalization and time to first rehospitalization for any reason. The statistical software package SPSS will be used for analysis. P-values <0,05 will be considered statistically significant.

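### Allocation is balanced by hospital, but no named between-group test accounts for hospital; if hospital predicts outcome, the tests are mildly conservative and some precision is lost

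*Protocol article*

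**What the plan says.** On allocation, the Study design section has 1:1 assignment: "Patients are randomized in equal proportions to one of two groups". The same section, in the text after Figure 1, gives the sites: "Patients are recruited from the Cardiology Departments of three Belgian hospitals". It also sets a floor on their size: "Each site recruits at least ten patients". The Randomization section adds the blocking: "Block randomization is used to ascertain equal distribution of patients in the intervention and control group in the different recruiting hospitals". It does not use the word stratified, but blocking within hospital is the natural reading. Block size is not given.

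On analysis, the Statistical analysis section names one between-group test for each situation:

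- Non-normal continuous data: "the Mann–Whitney U-test will be used for the comparison between groups".
- Normal continuous data: "the One Way ANOVA repeated measures test will be used for both between and within group analysis".
- Time to first rehospitalization: "Kaplan-Meier plots and log-rank tests will be used to compare censored time-to-event data".

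Hospital appears in none of them. The only adjustment stated anywhere is for baseline, in the Study endpoints section, and it covers three questionnaire scores (HeartQol, IPAQ, EQ-5D).

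**The concern.** Balancing the arms within each hospital removes hospital-to-hospital differences from the treatment comparison. A test that leaves hospital out still counts those differences as noise. The reported standard error then exceeds the true sampling spread of the estimate, p-values come out too large, and part of the precision gained by the blocking goes unused.

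Hospital could plausibly matter here. Each site runs its own recruitment and follow-up visits, those visits include the exercise test that yields VO2 peak, and both arms receive center-based rehabilitation. What is at stake is precision and a little power, not protection against false positives.

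**Working it through.** **Inputs from the protocol article.** Three hospitals and at least ten patients per site (Study design); 1:1 allocation; significance at 0.05; power 95%, total 140 and dropout 30% (Sample size). Evaluable patients: 140 × 0.70 = 98, or 49 per arm.

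**Assumed input.** r, the share of outcome variance lying between hospitals. The documents give no figure, so r = 0 to 0.20 is shown.

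**The plan's own figure.** The total of 140 cannot be reproduced from the stated inputs, because the 20% effect size comes without a standard deviation. Read as a relative difference, it gives 138 to 143 only if the standard deviation is back-solved at 27% to 27.5% of the mean (two-sided). The check below needs only the stated 95% power, so it does not depend on settling this.

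**Formulas** (outcome at one time point, total variance 1, arms balanced within hospital, two-sided 0.05):

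- Reported standard error without hospital: √(4/N). True spread of the estimate: √(1−r) × √(4/N). The reported error is therefore too large by 1/√(1−r) − 1.
- Type I error without hospital: 2 × [1 − Φ(1.96/√(1−r))].
- For 95% power, the non-centrality is 1.960 + 1.645 = 3.605, so the standardised effect with 98 patients is 3.605 × √(4/98) = 0.728.
- Power without hospital: Φ(1.645/√(1−r)). Power with hospital: Φ(3.605/√(1−r) − 1.960).

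Example at r = 0.10: 1/√0.90 = 1.054, so the standard error is 5.4% too large. The effective critical value is 1.96 × 1.054 = 2.066, which gives type I error 0.039. Power is Φ(1.734) = 95.9% without hospital and Φ(1.840) = 96.7% with it.

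| r | SE too large by | Type I, hospital ignored | Power ignored | Power adjusted | Points lost |
|---|---|---|---|---|---|
| 0 | 0% | 0.050 | 95.0% | 95.0% | 0 |
| 0.01 | 0.5% | 0.049 | 95.1% | 95.2% | 0.1 |
| 0.05 | 2.6% | 0.044 | 95.4% | 95.9% | 0.5 |
| 0.10 | 5.4% | 0.039 | 95.9% | 96.7% | 0.8 |
| 0.20 | 11.8% | 0.028 | 96.7% | 98.1% | 1.4 |

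**Check by simulation.** 98 patients, blocks of 4 within hospital, hospital sizes 33/33/32 or 78/10/10, with 20,000 null runs and 5,000 power runs per setting. A t-test ignoring hospital was compared with a linear model including it.

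- At r = 0.10, type I error was 0.038 to 0.042 ignoring hospital and 0.049 to 0.050 adjusting for it. Power was 95.7–95.9% and 96.4–96.8%. The estimate's actual standard deviation was 0.192–0.193, against an average reported standard error of 0.202 without hospital and 0.191 with it.
- At r = 0.20, type I error was 0.029 to 0.031 ignoring hospital. The simulated power loss was 1.7 points, against 1.4 from the formula. Each simulated power carries a Monte Carlo standard error of 0.2 to 0.3 points.

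**Repeated measures.** If hospital k shifts a patient's VO2 peak by a constant h_k at every visit, the change from baseline is free of h_k, so that shift drops out of a group-by-time contrast. Only hospital differences in change remain, and r must then be read as their share of the variance of change. With baseline as a covariate with slope β, (1−β) × h_k remains, so most of a stable difference goes when β is near 1.

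The table applies to a single-time-point comparison of means. No figure was derived for the rank or log-rank tests; the same reasoning gives the direction but not the size.

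**The case against.** The strongest reply is that the article is condensed. It names families of tests in one paragraph, never says they are unstratified, and a full protocol or analysis plan might add hospital. It is right that nothing excludes hospital, and a reader should not infer a deliberate decision to ignore it. But this is more than missing detail: specific tests are fixed, Mann-Whitney and log-rank as named do not use hospital, and Table 1 points to this section for both statistical-methods items.

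Second, the harm is conditional. With r = 0 nothing is lost, and with r = 0.01 almost nothing. This stands.

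Third, for normal data the primary endpoint goes to repeated-measures ANOVA, where a stable hospital difference cancels from the group-by-time term. This also stands. The table is closest to a group main effect or a comparison of follow-up values, and is an upper guide elsewhere.

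Fourth, the formula treats balance within hospital as exact. The Randomization section allows a second randomization for patient characteristics without saying that the hospital blocks are kept, and 30% dropout is expected. If balance is disturbed, the unadjusted test is less conservative than shown. Hospital then enters the estimate itself, so the case for adjusting remains.

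A reader might go further and infer that the trial's p-values are invalid, or that its intervals will certainly be too wide. The documents support neither. The direction is conservative, and no passage shows that hospital predicts outcome.

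**Conclusion.** The mismatch is real and modest. The arms are balanced within three hospitals, and no between-group test named in the Statistical analysis section accounts for hospital. If hospital explains up to 20% of the variance of a single-time-point outcome, ignoring it gives the conservative distortion tabulated above, with a power cost small enough to leave the 95% target intact. With balanced arms there is no bias, and false positives are not inflated.

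This rests on reading the blocking as within hospital, on near-exact balance, and on an assumed range for r that the documents neither support nor rule out. The point is a nearly free improvement in precision, not a threat to validity.

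**What to change.** Add a sentence to the analysis section, before the data are analysed, saying that between-group comparisons account for hospital:

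- VO2 peak: include hospital (3 levels) as a fixed effect, alongside baseline VO2 peak.
- Continuous outcomes now assigned to Mann-Whitney: use the hospital-stratified rank test (van Elteren).
- Both time-to-event endpoints: stratify the log-rank test by hospital.

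The cost is 2 degrees of freedom in the linear model (without the baseline term, residual degrees of freedom go from 98 − 2 = 96 to 98 − 4 = 94). No new data or change in conduct is needed. If a site recruits only about ten patients, roughly five per arm, its stratum will add little information to the stratified rank and log-rank tests. The Trial status section reports the study as ongoing, so the change can still be prespecified.

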### Outcome assessments

At entry of study a complete medical history, clinical assessment (including measurement of body mass index, waist circumference, blood pressure and heart rate) and treatment scheme are collected. A transthoracic echocardiography (TTE) evaluating LV systolic function (using Simpson’s method and/or eye balling), LV diastolic function (E/A ratio, DT, IVRT and pulmonary venous flow curves) and presence/absence of increased left atrial filling pressures (average E/E’) is planned, when no recent TTE (performed < 6 months earlier) is available. Every patient performs a maximal cardiopulmonary exercise test (CPET) with breath-by-breath gas exchange analysis. The criteria for defining maximal CPET are an achieved heart rate > 85 % of the maximal predicted heart rate, an achieved Respiratory Exchange Ratio (RER) > 1,1, and/or achieving a plateau on the VO2 curve. During CPET, we will record RER, resting and maximal heart rate, resting and maximal systolic and diastolic blood pressure, resting and maximal rate pressure product, VO2 peak, maximal work load, ventilatory anaerobic threshold, respiratory compensation point and the oxygen uptake efficiency slope. We will use the recommendations provided by Wasserman et al. to predict VO2 peak and to calculate % of predicted VO2 peak [10]. Fasting blood samples are taken, to determine blood glucose, HbA1c, CRP level and lipid profile. Patients are asked to complete a quality of life questionnaire (HeartQol), a questionnaire to assess self-reported physical activities (IPAQ) and the EQ-5D questionnaire. After randomization, study visits were scheduled after 6 weeks as well as at the end of study period. During these visits, clinical assessment, treatment scheme collection and maximal CPET are performed. Patients are again asked to complete the HeartQol, IPAQ and EQ-5D questionnaires. Blood sampling is only repeated after study completion (Fig. 1).

### Study intervention

Patients in the intervention group are provided with an internet-based telerehabilitation program in addition to conventional center-based CR. The telerehabilitation program is composed of physical activity telemonitoring (Yorbody accelerometer) in addition to dietary, smoking cessation and activity telecoaching.

